**Methods:**

The PRiVENT intervention is a prospective, mixed-methods interventional, multicentre study with a parallel comparison group selected from insurance claims data of the health insurer Allgemeine Ortskrankenkasse Baden-Württemberg (AOK-BW) conducted in Baden-Württemberg, Germany, over 24 months. Four weaning centres supervise 40 intensive care units (ICUs), that are responsible for patient recruitment. The primary outcome, successful weaning from IMV, will be evaluated using a mixed logistic regression model. Secondary outcomes will be evaluated using mixed regression models.

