### Outcomes

The primary outcome is defined as the successful weaning from IMV of high-risk patients before discharge from the ICU or from the weaning centre.

Secondary outcomes are:Time from intubation to successful weaning during hospitalisation in hours on the ventilator.Successful weaning for at least 48 consecutive hours in the intervention group, regardless of patient ventilatory status at discharge.Mortality during the in-patient stay.Re-hospitalisation for the same indication within 30 days of discharge.Use of emergency services within 30 days and within 3 months of discharge.No need for IMV 3 months after discharge.Utilisation of rehabilitation services within 3 months of discharge.Re-hospitalisation with IMV within 6 months of discharge.Mortality at 6 and 12 months.

Patients who either die before successful weaning, require continued IMV at hospital discharge, or cannot be discharged within 6 months of starting IMV or by 30th June, 2023, are considered weaning failures. June 30th, 2023, is the last date for which comparison data are available and thus represents a pragmatic threshold to ensure comparability of the intervention and comparison groups.

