#### Comparison group of the intervention study

The comparison group will be matched from AOK-BW health care claims data provided by hospitals in Baden-Württemberg. Because of the necessary processing in AOK-BW the data will be available from late 2019 to late 2023. Only patients ventilated for at least 96 h will be included in the comparison group. Patient data will then be reviewed for the other eligibility criteria and the risk of long-term IMV will be assessed by the prognostic model. Patients admitted to the hospital with acute COVID-19 pneumonia are automatically classified as high-risk. The group of patients used for the primary assessment of the intervention effect will be additionally limited to patients who do not die within 11 days of starting ventilation. This ensures comparability with the intervention group and corresponds to the screening period in the intervention group.

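### The 30 June 2023 clause counts administrative censoring as weaning failure in the primary endpoint, and the reason given for that date conflicts on its face with the stated claims-data window

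*Protocol article*

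**What the plan says.** The primary outcome (Outcomes section) is "successful weaning from IMV of high-risk patients before discharge from the ICU or from the weaning centre". The same section then defines failure. Besides death before weaning and continued IMV at hospital discharge, it lists patients who "or cannot be discharged within 6 months of starting IMV or by 30th June, 2023, are considered weaning failures". The reason given is that "June 30th, 2023, is the last date for which comparison data are available and thus represents a pragmatic threshold", chosen to keep the two groups comparable.

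The section on the comparison group gives a different window for the claims: "Because of the necessary processing in AOK-BW the data will be available from late 2019 to late 2023".

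No recruitment end date appears. The abstract says the study is "conducted in Baden-Württemberg, Germany, over 24 months". The Study objectives section starts the project in July 2020 and uses the first 12 months for preparation.

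The Final analysis section counts as failures the intercurrent events that would prevent weaning, allows multiple imputation of missing values, and names sensitivity analyses for the imputation strategy, the 7-day window and the covariates. None of those named concerns the calendar cut.

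**The concern.** The six-month limb gives every patient the same time in which to succeed. The calendar limb does not. For IMV starts up to about 31 December 2022 the six-month limb is reached first and the calendar limb is idle. For later starts the time allowed shrinks to whatever remains before 30 June 2023. A patient ventilated from May 2023 and still an in-patient on 30 June is coded like one who has not been discharged after six months. As written, there is no exception for someone already off the ventilator but not yet discharged.

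The end of a data extract does not prevent weaning, so the intercurrent-event rule does not justify the coding. At stake are extra failures in both groups, a smaller contrast and less power. If the claims in fact cover care to late 2023, the only reason given for the clause also falls away.

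**Working it through.** **The plan's own figure.** Inputs from the Sample size section: 1,495 per group, cluster size 25, ICC 0.1, drop-out 10.6%, failures 20% vs 30%, alpha 5% (taken as two-sided).

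- Design effect: 1 + (25 − 1) × 0.1 = 3.4.
- Effective size: 1,495 / 3.4 = 439.7; × (1 − 0.106) = 393.1.
- Power: Φ[(0.10 − 1.96 × √(2 × 0.25 × 0.75 / 393)) / √((0.16 + 0.21) / 393)] = Φ[(0.10 − 0.0605) / 0.0307] = 90.1%.

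The stated 90% reproduces. It makes no allowance for the calendar clause.

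**Could the clause bite?** July 2020 + 12 months of preparation + 24 months = about the end of June 2023. This allows intake up to the cut but does not establish it.

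**Share of patients cut early.** Assumptions, none of them in the article: uniform intake over T = 730 days ending g days before 30 June 2023; lognormal stay from IMV start with median 30, 45 or 60 days and log-SD 0.6. With S(u) the probability of still being an in-patient u days after IMV start, the share still in hospital at the cut who would have been discharged by day 182 is

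f = (1/T) × ∫ from g to 182 of [S(u) − S(182)] du.

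| Intake ends | f, median 30 d | 45 d | 60 d |
|---|---|---|---|
| 30 June 2023 | 4.9% | 7.1% | 8.8% |
| 60 days earlier | 0.4% | 1.2% | 2.3% |
| 90 days earlier | 0.1% | 0.4% | 0.9% |
| by December 2022 | 0 | 0 | 0 |

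**Effect on the contrast, same calendar intake in both groups.** If those cut would otherwise have failed at their group's planned rate p, the observed failure rate is p + f(1 − p), and the difference becomes 10 × (1 − f) points. For intake to the last day:

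| Median stay | Failures | Difference | Power (393 per group) |
|---|---|---|---|
| 30 d | 23.9% vs 33.4% | 9.5 points | 84% |
| 45 d | 25.7% vs 35.0% | 9.3 points | 81% |
| 60 d | 27.0% vs 36.2% | 9.1 points | 79% |

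An exponential stay with mean 20 to 60 days gives the same picture: f = 2.7 to 6.6%, difference 9.7 to 9.3 points, power 87 to 82%.

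**Unequal calendar intake (hypothetical).** If comparison patients were spread over about 45 months up to the cut, f there would be 2.6, 3.8 or 4.7%. At the 60-day median: 0.20 + 0.80 × 0.088 = 27.0% vs 0.30 + 0.70 × 0.047 = 33.3%, a difference of about 6.2 points and power of about 48%. At the 30-day median: 7.9 points and 70%.

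**The two data end dates.** Outcomes: comparison data stop on 30 June 2023. Comparison-group section: data from late 2019 to late 2023. Read as dates of care, both cannot be true.

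**The case against.** The rule is disclosed, applies to both groups and has a stated purpose. The effect turns on an unstated date and fades fast: if intake closed 60 days before the cut, at most about 2% are affected. Those cut are also long-stayers, whose chance of weaning is probably below average, so the formula above probably overstates the false failures. All of this stands, and it limits the size. It does not make a data cut an outcome.

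The date conflict may be loose wording. A processing lag would fit care dates ending in June 2023 with delivery in late 2023. Against that, a late-2019 start precedes the project itself and reads more naturally as data coverage. The point needs clarifying; it is not a proven contradiction.

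Three stronger readings are tempting and are not supported:

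- **The intervention group is hit harder.** This needs either comparison patients from a longer calendar period or longer stays after transfer to a weaning centre. The article calls the comparison group parallel, and claims from late 2019 may serve only as pre-admission history. It says nothing on whether transfer lengthens or shortens stay. Even the direction is open: with intervention intake closing three months early and comparison intake from December 2019 to the cut, the exponential-stay calculation widens the difference to 11.0 to 11.8 points.
- **The effect could be reversed.** Even the hypothetical unequal case leaves about 6 of the 10 planned points.
- **Twelve-month mortality is lost in the comparison group.** The outcome "Mortality at 6 and 12 months" would be cut short for late entrants only if 30 June 2023 is the true end of the data. The Final analysis section already plans survival methods, which accommodate censoring, for time-to-event endpoints.

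**Conclusion.** The point holds in this form. The failure definition turns administrative censoring into primary-endpoint failures for IMV starts after about 31 December 2022, and the date behind it must be reconciled with the claims window stated elsewhere. The effect ranges from nil (intake closed by December 2022) to about 5 to 9% of patients cut early (intake to 30 June 2023). In that worst case, with equal calendar intake, the contrast is diluted to 9.1 to 9.5 points and power falls to about 79 to 84%. This rests on assumed uniform intake, assumed lengths of stay and average weaning rates among those cut. It also takes the rule to mean still being an in-patient, because the section refers both to discharge from the ICU or weaning centre and to discharge from hospital. How recent a start can be is bounded by the 96-hour entry criterion and, for comparison patients in the primary assessment, by survival to day 11. The sample size calculation itself is not in error.

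**What to change.** 1. State the last date of care covered by the comparison data and the date recruitment closes, and make the two sections agree.
2. If the data cover six months after the last IMV start, drop the calendar limb and apply the six-month rule alone to everyone. For June 2023 starts this needs data to the end of December 2023, which the words late 2023 do not guarantee.
3. Otherwise, treat patients still in hospital at the cut with under six months of observation as administratively censored or missing, using the multiple imputation already planned. Keep two sensitivity analyses: failure coding as now written, and restriction to IMV starts by 31 December 2022 in both groups.

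The cost is wording and a little more analysis. Restriction is better not made the primary analysis. With uniform intake to 30 June 2023 it drops up to 6/24 = 25% of patients, leaving 1,495 × 0.75 = 1,121 per group. On the protocol's assumptions:

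- cluster size kept at 25: 1,121 / 3.4 × 0.894 = 295 effective, power about 80%;
- cluster size reduced to 18.75: design effect 1 + 17.75 × 0.1 = 2.775, 1,121 / 2.775 × 0.894 = 361 effective, power about 88%.

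Both compare with the planned 90%.

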### Intervention elements

#### Prognostic model

Using predictive modelling methods, a prognostic model for prolonged IMV and weaning failure was developed by aQua and Thoraxklinik Heidelberg in several steps. First, a systematic literature review of risk factors associated with prolonged IMV and weaning failure was conducted [30]. Second, based on health care claims data from the AOK-BW, characteristics of in-patients were exploratively identified that had shown an empirical association with an increased risk of subsequent long-term IMV in bivariate analyses. The identified potential predictors were then tested for their predictive effect in multivariable logistic regression models. The goal of this modelling procedure was to identify patients eligible for the PRiVENT intervention. During the intervention patients will be screened and if they are eligible for the study their risk for prolonged IMV and weaning failure will be assessed by the prognostic model after inclusion.

#### Weaning board

After patients are classified into the high-risk group by the prognostic model, the baseline data form is completed in an electronic case report form (eCRF) and submitted to the weaning centre by the ICU. From the weaning centre side, the weaning board consists of at least one respiratory physician with expertise in weaning and one respiratory therapist. Participation of the ICU and other specialists takes place as needed. The weaning board should take place twice a week, at least once a week in the weaning centre. Colleagues from the cooperating ICU can take part in person or via telecommunication. The board’s assessment and recommendations will be communicated to the cooperating clinic pseudonymised via electronic fax or email. The goal is an individualised treatment recommendation for the ICU after an interdisciplinary discussion of the current case. Re-presentations can be made using the progress form. More detailed information can be found in the online Supplement.

#### Weaning consult

The weaning consult is defined as an interdisciplinary case discussion by the PRiVENT weaning centre team with the PRiVENT ICU practitioners. Preferably, the weaning consult takes place at bedside. The first weaning consult of a patient should be performed by the physician and respiratory therapist of the PRiVENT weaning centre within one week of inclusion. For further consults it is sufficient if one of the two is on site. In collaboration with the PRiVENT ICU staff, measures are discussed and a follow-up appointment is made as necessary.

#### Discharge management

As part of PRiVENT’s discharge management, all high-risk patients are followed-up with a structured interview five to eight weeks after discharge by telephone by a member of the study office at the Thorax Clinic Heidelberg. There is scientific evidence that monitoring patients after hospitalisation can allow early detection of complications and avoid re-hospitalisation [31].

#### Interprofessional quality circles, benchmarking & feedback reports

Quality circles are performed by each weaning centre and are interactive discussions of smaller groups, ideally no more than eight to 15 participants. A trained moderator (respiratory physician or respiratory therapist) leads the topic-centred discussion among participating colleagues. Positive and negative aspects of current processes are identified in order to initiate improvements. New findings are recorded and concrete measures are developed to be implemented for quality improvement. The latter are reviewed as part of the final evaluation. In PRiVENT quality circles take place every six month in person or online and take about one to two hours. Participants include staff from the cooperating ICU.

#### E-learning & training

Seven e-learning modules on weaning and corresponding case studies have been developed. These are made available online to the health care professional (physicians and nurses) participating in the study programme via a personal login code. The number and distribution of users in regard to the cooperating clinic are documented and evaluated. In addition, each weaning centre provides additional training once during the intervention phase.

#### Public relations and patients’ involvement

PRiVENT’s public relations work reaches out to relatives of ventilated patients, high-risk patients, medical professionals, and the general public. PRiVENT aims to educate the general public about the options and positive effects of weaning to minimise the risk of long-term IMV. A project website has been established with blog posts and a podcast series to provide reliable and trustworthy information. The information is published on high-reach platforms, such as Facebook, Instagram, Spotify and YouTube. Additionally, there is a cooperation with “Gesundheitstreffpunkt Mannheim”, a charitable organization with the objective to improve patients’ information and support groups.

### Recruitment of weaning centres and intensive care units

Only DGP (German Respiratory Society)-certified weaning units in BW are eligible to participate as weaning centres. All ICUs in BW that are not recruited as weaning centres can participate as ICUs.

### Recruitment of patients

#### Intervention study experimental group

The experimental group of the intervention study will consist of patients recruited from PRiVENT ICUs. All patients in participating centres on IMV between 96 h and 11 days will be screened for eligibility. This timeframe has been chosen pragmatically to ensure timely assignment of eligible patients to the intervention. Patients who fulfil the eligibility criteria and have given informed consent to participate in the study can be included. As invasively ventilated patients are usually not capable of giving consent, their legal guardian will be informed instead. After undergoing the prognostic model that classifies patients into high- and low-risk groups for long-term IMV, high-risk and all COVID-19 patients will be assigned to the intervention.

Inclusion criteria:

≥ 96 h of invasive ventilationno more than 7 days have passed since the patient completed their 96th hour of invasive ventilation≥ 30 years old≥ 1 comorbidity and/or acute Covid-19 pneumonianot suffering from any neuromuscular disease without weaning potential

No further exclusion criteria.

The time schedule of the patients’ journey can be found in the Supplement.

#### Comparison group of the intervention study

The comparison group will be matched from AOK-BW health care claims data provided by hospitals in Baden-Württemberg. Because of the necessary processing in AOK-BW the data will be available from late 2019 to late 2023. Only patients ventilated for at least 96 h will be included in the comparison group. Patient data will then be reviewed for the other eligibility criteria and the risk of long-term IMV will be assessed by the prognostic model. Patients admitted to the hospital with acute COVID-19 pneumonia are automatically classified as high-risk. The group of patients used for the primary assessment of the intervention effect will be additionally limited to patients who do not die within 11 days of starting ventilation. This ensures comparability with the intervention group and corresponds to the screening period in the intervention group.

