#### Final analysis

The primary outcome, successful weaning before discharge, will be evaluated using a mixed logistic regression model including treatment group, age, gender, acute COVID-19 pneumonia, pre-existing medical conditions via the Charlson Comorbidity Index (continuously) [33], number of ventilation cases of the centre, dependency on ventilatory assistance for at least 3 month within 1 year before admission (with tracheostomy vs without tracheostomy vs none), tracheostomy within 96 h of intubation, extracorporeal support (yes/no), and centre as a random intercept. The analysis population for the primary endpoint will be restricted in order that a possible bias due to the selection effect of the screening window will be minimized. If necessary, missing values will be imputed via a multiple imputation approach. For patients included into the analysis population, intercurrent events (such as death) which would prevent patients’ successful weaning will be counted as weaning failures. A number of sensitivity analysis will be conducted to investigate the impact of the imputation strategy, the 7-day inclusion window, and the choice of covariates.

The analysis of secondary outcomes will include the calculation of appropriate summary measures of the respective empirical distributions (mean, standard deviation, median, interquartile range, minimum and maximum for continuous variables, and absolute and relative frequencies for categorical variables), as well as descriptive *p*-values. In addition, similar mixed models as described for the primary outcome will be used, logistic models for categorical outcomes and linear models for continuous outcomes. Time to event endpoints will be analysed using methods from survival analysis, including Kaplan–Meier estimates, log-rank tests and shared frailty models similar to the primary analysis model. As appropriate, graphical methods will be used to visualise the results. Missing data in secondary outcomes will not be imputed.

In an explorative analysis, clinical data collected within the trial will be used in to identify potentially relevant factors which could help to supplement the developed prognosis model. To this end, an elastic-net approach, as well as decision-tree based models will be used.

A detailed statistical analysis plan will be set up prior to the final analysis. R version 4.0.2 or higher (www.R-project.org) will be used to carry out the analyses.

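### The day-11 survival restriction is written only for the primary endpoint, so the mortality outcomes, read as written, set patients alive at inclusion against a comparison group that still contains deaths before any possible enrolment

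*Protocol article*

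**What the plan says.** The Comparison group section of the protocol article builds the claims-data group in two steps. The base condition is: "Only patients ventilated for at least 96 h will be included in the comparison group". After the other eligibility criteria and the risk model are applied, the group "used for the primary assessment of the intervention effect will be additionally limited to patients who do not die within 11 days" of starting ventilation. The stated reason is: "This ensures comparability with the intervention group and corresponds to the screening period in the intervention group".

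The Final analysis section repeats the scope: "The analysis population for the primary endpoint will be restricted in order that a possible bias due to the selection effect of the screening window" is minimised. The sensitivity analyses on the 7-day inclusion window stand in that same primary-outcome paragraph.

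The Outcomes section lists "Mortality during the in-patient stay" and "Mortality at 6 and 12 months" as secondary outcomes. The secondary-analysis paragraph carries over the type of model and adds Kaplan–Meier, log-rank and shared frailty methods. It states no survival restriction, landmark or delayed entry.

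On the intervention side, the Recruitment of patients section screens patients who have been on invasive ventilation (IMV) for between 96 h and 11 days. Inclusion needs consent, usually through a legal guardian.

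**The concern.** The plan recognises that the screening window selects survivors and corrects for it, but the correction is attached to one endpoint. Mortality is where early deaths act most directly.

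Take a patient who dies on day 7. In a participating ICU, if not yet included, this patient never enters the intervention group. In the claims data the same patient meets the 96 h condition. The primary assessment removes this patient, but nothing written removes the death from the mortality outcomes. None of the covariates listed for the model records survival to enrolment, so adjustment does not repair this. Survival methods without delayed entry would carry the same bias.

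Mortality is the natural safety check on a weaning programme. A difference produced by the entry rules could be read as a benefit or could hide part of a harm.

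**Working it through.** **The plan's own figure.** Design effect 1 + (25 − 1) × 0.1 = 3.4. Then 1,495 / 3.4 = 439.7, and 439.7 × (1 − 0.106) = 393.1. A two-sided 5% chi-squared test of 20% against 30% with 393 per group has power 90.1%, so the stated 90% reproduces. It is used here only for scale: at 30% mortality the standard error of a difference is √(2 × 0.3 × 0.7 / 393) = 0.033, or 3.3 points. That borrows an intra-class correlation assumed for weaning.

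**Inputs for the bias.** From the document: the window from 96 h to day 11, which is 7 days. Everything else is assumed, because the document gives no mortality or early-weaning rate:
- M = 0.30, in-patient mortality among all patients ventilated at least 96 h, the same in both groups (no true effect).
- e = share of the group dying in the window. If 20%, 35% or 50% of deaths fall there, e = 0.06, 0.105 or 0.15.
- w = share weaned in the window (0 to 30%), with 5% later mortality.
- Deaths and weanings are spread evenly over the window.
- q = chance that such an event precedes enrolment. Enrolment uniform over the window: q = 0.5. Early enrolment (exponential delay, mean 2 days, capped at 7): q = 2(1 − e^(−3.5)) / 7 = 0.277, where this e is the exponential base.

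**Formula.** Comparison mortality = M. Intervention mortality = (M − eq − 0.05wq) / (1 − eq − wq).

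Example with uniform enrolment, e = 0.15, w = 0: (0.30 − 0.075) / (1 − 0.075) = 0.243, a gap of 5.7 points. With e = 0.06, w = 0.20: (0.30 − 0.03 − 0.005) / (1 − 0.03 − 0.10) = 0.305, a gap of −0.5.

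Artificial difference in points (positive favours the intervention):

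| Enrolment | w | e = 0.06 | e = 0.105 | e = 0.15 |
|---|---|---|---|---|
| Uniform | 0 | 2.2 | 3.9 | 5.7 |
| Uniform | 10% | 0.9 | 2.7 | 4.6 |
| Uniform | 20% | −0.5 | 1.4 | 3.3 |
| Uniform | 30% | −2.0 | −0.1 | 1.9 |
| Early | 0 | 1.2 | 2.1 | 3.0 |
| Early | 10% | 0.5 | 1.4 | 2.4 |
| Early | 20% | −0.2 | 0.7 | 1.7 |
| Early | 30% | −1.0 | 0.0 | 0.9 |

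A simulation under the same assumptions agrees to within about 0.1 point.

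**Later mortality.** With w = 0 the gap equals eq(1 − M) / (1 − eq). The same early deaths stay in the 6- and 12-month outcomes, and the gap shrinks only in proportion to 1 − M. If M were 0.50, the 5.7 points would become 0.075 × 0.5 / 0.925 = 4.1.

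**Restricting the comparison group alone.** Comparison mortality becomes (M − e) / (1 − e), while enrolled patients can still die before day 11. With uniform enrolment and w = 0: 0.255 against 0.278 at e = 0.06, and 0.176 against 0.243 at e = 0.15. That is 2.3 to 6.7 points against the intervention.

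**Day-11 landmark in both groups, alive only.** With w = 0 both groups have (M − e) / (1 − e) and the gap is zero. With early weaning a residue remains, because comparison patients weaned before enrolment stay in. At e = 0.06, w = 0.10, q = 0.5: (0.24 − 0.0025) / (0.94 − 0.05) = 0.267 against 0.24 / 0.94 = 0.255, or 1.2 points against the intervention.

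**The case against.** The strongest reply is that no sentence says the secondary outcomes use the unrestricted group. The article condenses a fuller protocol, announces a detailed analysis plan, and shows that its authors know of the window's selection effect. It also says the comparison group will be matched, without naming the variables. The unseen plan may well settle the mortality population. This stands as a limit on certainty. It does not remove the point: the article does more than stay silent, because it creates a base group and an additionally limited one, and assigns the limited one to the primary endpoint in two places.

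A reader might go further and infer that the intervention is favoured by construction. The documents do not support that. Early-weaned comparison patients act in the opposite direction, and in several rows of the table the gap vanishes or reverses. The window was also chosen for timely assignment, which points to the smaller figures.

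A reader might also turn the largest gap into an inflated false-positive rate: at 5.7 points and a standard error of 3.3, about 41% instead of 5%. That needs uniform enrolment, no early weaning and half of all deaths inside the window. It also matches no planned confirmatory test, because secondary p-values are declared descriptive.

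Nor would a mortality harm go wholly unseen. Death before successful weaning counts as failure in the primary analysis.

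**Conclusion.** The point holds in a limited form. As written, the restriction that the plan itself calls necessary for comparability does not reach the three mortality outcomes. Their comparison then mixes patients selected for being alive and ventilated at inclusion with a group not so selected.

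The likely direction favours the intervention but is not certain. Under assumed 30% mortality and no true effect, the in-patient difference runs from about zero or slightly reversed (−2.0 only at 30% early weaning) to 5.7 points. With early enrolment and up to 20% weaned early it is about 0 to 3 points. All rates behind these figures are assumptions, and matching is not modelled. The primary analysis and its power are untouched. What is at risk is the mortality estimate and how it is read.

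**What to change.** In the Comparison group and Final analysis sections, and in the analysis plan, state that the mortality outcomes use the same time origin and entry condition in both groups. Count time from the start of ventilation, with delayed entry at the inclusion day. Require comparison patients to be alive and still ventilated on a matched ventilation day, or on a day drawn at random from the observed inclusion days. This aligns both early deaths and early weaning.

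As a simpler sensitivity analysis, apply a day-11 landmark to both groups, conditioned on being alive only. Do not also require patients to be on IMV at day 11: the intervention can begin from 96 h, so weaning by then may already be its effect. State that the alive-only landmark leaves the early-weaning residue shown above. Do not restrict the comparison group alone, as this over-corrects. Keep the unrestricted comparison as descriptive.

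Cost: a few sentences and one more population flag. Deaths before entry drop out, so fewer early deaths are analysed. Ventilation duration in days is needed from the claims data, and its availability should be confirmed before the rule is fixed.
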